## Abstract

Tensiomyography measures the radial displacement of a muscle during an electrically evoked twitch contraction. The rate of muscle displacement is increasingly reported to assess contractile properties. Several formulas currently exist to calculate the rate of displacement during the contraction phase of the maximal twitch response. However, information on the reproducibility of these formulas is scarce. Further, different rest intervals ranging from 10 s to 30 s are applied between consecutive stimuli during progressive electrical stimulation until the maximum twitch response. The effect of different rest intervals on the rate of displacement has not been investigated so far. The first aim of this study is to investigate the within and between-day reliability of the most frequently used formulas to calculate the rate of displacement. The second aim is to investigate the effect of changing the inter-stimulus interval on the rate of displacement. We will determine the rectus femoris and biceps femoris rate of displacement of twenty-four healthy subjects’ dominant leg on two consecutive days. The maximum displacement curve will be determined two times within three minutes on the first day and a third time 24 h later. On day two, we will also apply three blocks of ten consecutive stimuli at a constant intensity of 50 mA. Inter-stimuli intervals will be 10 s, 20 s or 30 s in each block, respectively, and three minutes between blocks. The order of inter-stimulus intervals will be randomized. This study will allow a direct comparison between the five most frequently used formulas to calculate the rate of displacement in terms of their reproducibility. Our data will also inform on the effect of different inter-stimulus intervals on the rate of displacement. These results will provide helpful information on methodical considerations to determine the rate of displacement and may thus contribute to a standardized approach.

## Introduction

A muscle twitch is the contractile response to a single electrochemical signal of the nervous system or artificial electrical stimulation of the muscle. As such, a twitch provides information on muscle contractile properties and the functioning of the excitation-contraction coupling process. Tensiomyography (TMG) measures the radial displacement of a muscle belly during an electrically stimulated isometric twitch response. From the radial displacement curve, spatial and temporal parameters are derived. The two most frequently reported parameters are the maximum displacement (Dm) and the contraction time (Tc) [1]. Dm provides information on skeletal muscle stiffness, morphological and structural changes [2–4]. Tc refers to the time interval between 10% and 90% of Dm and is correlated to the proportion of slow-twitch fibres [5–7]. Therefore, a shorter Tc is commonly associated with a higher contraction velocity [8–11].

TMG is an involuntary method that does not require any effort from the subject. Therefore it is frequently used to assess muscular function following fatiguing exercise [12–16] or the effectiveness of different recovery strategies [17–20]. Muscular fatigue causes a slowing of muscle contraction velocity, reversing as the muscle recovers from fatigue [21–24]. Consequently, an increase in Tc of a fatigued muscle which is reversed as the muscle recovers is expected. However, previous studies found no change [14] or even a decrease of Tc [16, 25] after fatiguing exercise. Several authors pointed out that changes in Dm inevitably lead to changes in Tc [25, 26]. Accordingly, changes in Tc should not be interpreted independently of changes in Dm.

As a result, an increasing number of studies reports the rate of displacement (Vc), i.e. the slope of the radial displacement-time curve. Several different formulas exist to calculate Vc but no consensus exists on the most suitable formula. Further, there is a lack of studies investigating the reproducibility of these formulas, as only two studies investigated the reliability of Vc so far. Lohr et al. [27] investigated the within and between-day reliability of Vc in the lumbar erector spinae muscle of healthy females and males, using this formula: Vc = 0.8*Dm / Tc. Vc in this study showed an excellent relative (intraclass correlation coefficient ICC > 0.90) and absolute (coefficient of variation CV < 8%) reliability. De Paula Simola et al. [28] investigated the between-day reliability of the following two formulas to calculate Vc in twenty male sports students: V_10_ = 0.1*Dm / t_10%_ and V_90_ = 0.9*Dm / t_90%_ [28]. Absolute reliability was higher in rectus femoris (RF) and biceps femoris (BF) (CV < 10%) compared to gastrocnemius lateralis (CV = 12.3% and CV = 11.3% for V_10_ and V_90_, respectively) [28]. Both formulas showed excellent relative reliability in all three muscles (ICC > 0.90) [28]. In addition to the formulas used in the two studies mentioned, two other formulas to calculate Vc have been frequently reported: Vc = Dm / (Td +Tc) [29] and Vc_rn_ = 0.8 / Tc [30]. The reproducibility of Vc calculated by these two formulas is still unclear. Therefore, information on the reproducibility of these two formulas is needed. Further, a direct comparison of all five formulas for calculating Vc in terms of their reproducibility within the same sample would help reach a consensus on a standardized approach.

Differences exist not only regarding the formulas used to calculate Vc, but also regarding the electrical stimulation procedure to determine the radial displacement curve from which Vc is calculated. In a systematic review about the reliability of TMG, Martín-Rodríguez et al. [1] found that previous studies mainly used an inter-stimulus interval (ISI) of 10 s or 15 s to avoid fatigue or post-tetanic potentiation. But they also stated a lack of studies investigating the optimal rest interval between consecutive stimuli [1]. To our knowledge, only two studies investigated the effect of different ISI on tensiomyographic parameters so far. One study investigated the effect of different ISI (30 s, 10 s, 5 s) on Dm and Tc of the RF muscle during ten consecutive stimuli at a constant intensity (50 mA) [31]. The results showed that Tc was not significantly affected by different ISI, whereas Dm was significantly greater using an ISI of 10 s than 30 s [31]. Notably, Tc decreased significantly during ten consecutive stimuli, irrespective of the ISI, whereas Dm was not affected [31]. However, Latella et al. [32] found no significant effect of ISI (10 s, 20 s) on Dm or Tc of the biceps brachii muscle. Consequently, they concluded that an ISI of 10 s is sufficient during five consecutive stimuli [32]. However, both of the studies mentioned above did not report Vc, so the effect of ISI during repeated stimulation on Vc is still unclear.

Therefore, the first aim of this study will be to investigate the within and between-day reliability of five different formulas to calculate Vc. The second aim will be to investigate the effect of different ISI during repeated stimulation on Vc, assessed by the example of M. biceps femoris and M. rectus femoris. We hypothesize that Vc will be affected by changing ISI during ten repeated stimuli at a constant intensity of 50 mA.

## Materials and methods

### Study design

This study will be a single group reliability study with repeated measurements within two consecutive days. The design of this study follows the recommendations for conducting and reporting diagnostic reliability studies provided in the quality appraisal of reliability studies (QAREL) checklist [33] and the guidelines for sex and gender equity in research (SAGER) [34].

### Ethical approval, registration and data availability

This study will be conducted in accordance with the Declaration of Helsinki [35]. The Ethics Committee of the Institute of Applied Training Sciences has approved this study (reference number: ER_2021.29.03_2). Eligible participants will be informed about all relevant aspects of this study and asked for their written consent before their enrolment. Upon in principle acceptance from the journal and before starting the recruitment and data collection, this study protocol will be preregistered. The preregistration including the accepted study protocol and supporting information will be openly available on the Open Science Framework platform at https://osf.io/4du2j/?view_only=ee7a4afb30514cb9a2e15381282dcec8. Once we finished the data collection and analysis, our data and the analysis code will be also openly available on this platform.

### Participants and setting

This study will be conducted at the Institute for Applied Training Science. We will include 24 women and men in this study, who will be required to meet the following inclusion criteria: healthy, aged between 18–40 years, physically active for a minimum of three times per week. In addition, we will describe the subjects’ physical activity level based on data collected using the short form of the International Physical Activity Questionnaire (IPAC-SF) [36]. Exclusion criteria will be the following: pregnancy, history of neuromuscular or musculoskeletal disorders, pain or injury in the lower limbs during the last six months, previous surgical treatment to the lower limbs, practising a specific sport on a professional level, taking prescribed medication, nontolerance or any contraindication to electrical stimulation using self-adhesive electrodes, and wearing an implantable medical device. Participants will be recruited from scientific staff and students from the Institute for Applied Training Science and the Sport Sciences Department of the University of Leipzig. To this end, we will promote the study through email distribution lists, flyers and word of mouth. Potential participants will receive an informal invitation.

### Experimental approach

We will determine the absolute and relative within- and between-day reliability of the five most frequently used formulas to calculate the rate of displacement of the RF and BF assessed via TMG. The RF and BF were selected as they are the most frequently investigated muscles within studies reporting Vc. We will also determine the effect of three different rest intervals between ten consecutive stimuli at a constant intensity on the rate of displacement. The number of stimuli is consistent with a previous study which showed that Tc decreased significantly with ten stimuli [31], and which served as the reference for our sample size calculation. Fig 1 schematically illustrates the study flow.

**Fig 1 pone.0262156.g001:**
[figure not shown]
Schematic illustration of the study flow. M1, M2, M3: Measurement time points 1,2,3, respectively, mA: Milliampere, ISI: Inter-stimuli interval.

A single rater with more than three years of experience performing TMG measurements will perform all tensiomyographic measurements across two consecutive days. The individual maximum radial displacement curve of both the RF and BF will be determined two times on the first day (M1, M2), separated by a three-minute pause, and a third time on the second day (M3), 24 h after the first measurement. On the second day and three minutes after the third measurement, we will apply three blocks of ten consecutive stimuli each. The rest intervals between consecutive stimuli in each block will be 10 s, 20 s and 30 s, respectively. The rest period between block 1, block 2 and block 3 will be three minutes, respectively. We will randomize the order of the three blocks with the different ISI for each participant.

On the first day, we will familiarize all participants with the electrical stimulation procedure by applying two stimuli with a duration of 1 ms each at 20 mA and 30 mA to the RF, followed by a three-minute rest before starting the actual measurement [31]. All measurements will be taken at the same time of the day, and a constant room temperature of 21° C. Participants will be asked to refrain from caffeine intake for 2 h preceding all measurements [37] and to avoid alcohol consumption and fatiguing exercise for 24 h before the start and during the trial to counteract possible confounding. Further, participants will be asked to record their total dietary intake during the 24 h before the first appointment and replicate their intake during the 24 h before the second visit [26] (S1 Appendix).

### Randomization and blinding

We will use an online program [38] and a block randomization procedure with four blocks of six unique numbers [39] to determine the order of ISI during repeated stimulations for each participant. To blind the rater from previous measurements, we will choose the settings of the TMG measurement software as not to display prior measurements.

### Sample size justification

Two different calculations were made to justify the sample size for this study. First, a precision-based calculation for the ICC of Vc was based on previous reliability studies [27, 28]. For this calculation, we used RStudio, Version 1.3.959 and the "Nest"-function from the "ICC" package version 2.3.0 [40]. Assuming the lowest ICC reported of 0.92 [28], two measurements per subject and an alpha level of 0.05, we will need 18 subjects to achieve the desired precision with a confidence interval of 0.15.

Second, to estimate how many subjects we will need to detect an effect of changing the interstimulus-interval on Vc, we used the raw data provided by Wilson et al. [31]. From those data, we calculated Vc_10-90%_ = 0.8 Dm / Tc and Vc_norm_ = 0.8 / Tc (S1 Table). As only Dm and Tc were included in those raw data, we could not apply the other three formulas. We performed a two-way (ISI x measure) repeated measures analysis of variance (ANOVA) to estimate the main effect of inter-stimulus interval on Vc_10-90%_ and Vc_norm_. We obtained effect sizes using RStudio and the "eta2_to_f"-function from the "effectsize" package [41] and calculated the sample size using the "wp.rmanova"-function from the "WebPower"-package [42]. For the sample size calculation, we assumed three groups, ten measurements per subject, an effect size f = 3.1 (Vc_10-90%_) and f = 1.6 (Vc_norm_), a nonsphericity correction coefficient of 0.7 (Vc_10-90%_) and 0.6 (Vc_norm_), an alpha level of 0.01, a power of 0.95 and a between effect, a total of 9 (Vc_10-90%_) subjects and 18 (Vc_norm_) subjects were needed. We confirmed the estimated sample size for the ANOVA by repeating the calculations for both Vc_10-90%_ and Vc_norm_ using g*power v3.1.9.2 [43]. Based on the results of both calculations for the ICC and the ANOVA and accounting for potential dropouts, we intend to recruit 24 subjects.

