### Statistical analysis

We will report Vc_0-10%_, Vc_0-90%_, Vc_10-90%_, Vc_norm_ and Vc_Dm/t90%_ for both the RF and BF descriptively as mean (M) and standard deviation (SD). All data will be checked for outliers via visual inspection of boxplots. Outliers will be defined as data points outside of three times the interquartile range. The normal distribution of all variables will be tested using the Shapiro-Wilk Test. To assess a systematic bias between M1-M2 and M1-M3, we will perform a two-tailed paired t-test, respectively [47].

For the assessment of relative reliability, we will calculate intra-class correlation coefficients (ICC, mean rating (k = 2), absolute agreement, two-way mixed-effects model) with 95% confidence intervals (CI) [48]. ICC scores lower than 0.5, between 0.5 and 0.75, between 0.75 and 0.9 or greater than 0.9 will be interpreted as poor, moderate, good or excellent reliability [48].

Absolute reliability will be quantified by calculating the standard error of measurement (SEM and SEM%), the minimal detectable change (MDC and MDC%) [49] and the CV [47], including the respective 95% CI’s. The SEM indicates the estimation precision of a measure and will be calculated as SEM = SD * √1-ICC [47]. The SEM% allows a comparison of different Vc calculations as it is unitless and will be calculated as SEM% = (SEM / M)* 100 [50]. The MDC presents the smallest difference between two measures that can be differentiated from measurement error and hence may be considered real [49]. Following Weir et al. [49], we will calculate the MDC as MDC = SEM * 1.96 * √2. The MDC% will be calculated as MDC% = (MDC/M) * 100 [50] to allow a comparison between different calculations of Vc independently of units. The CV will be calculated as CV = SD / M * 100 [47], whereby SD refers to the standard deviation and M to the mean of individual differences between M1 and M2 or M1 and M3. A CV > 10% will be interpreted as insufficient reliability with reference to previous studies investigating the reliability of tensiomyographic parameters [27, 51, 52].

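### The 18 subjects given for an ICC interval of width 0.15 rest on an optimistic large-sample formula: the single-measure ICC that was sized needs 21 to 22, and the ICC form to be reported is not the one sized

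*Protocol article*

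**What the plan says.** The section on sample size justification in the protocol article gives a precision calculation for the ICC, made with the Nest function of the R package ICC. Its inputs are "Assuming the lowest ICC reported of 0.92" and "two measurements per subject and an alpha level of 0.05", and its result is that "we will need 18 subjects to achieve the desired precision with a confidence interval of 0.15". A separate ANOVA calculation follows, from which "a total of 9 (Vc_10-90%_) subjects and 18 (Vc_norm_) subjects were needed". The section then combines both results and, "accounting for potential dropouts, we intend to recruit 24 subjects". No dropout rate is given.

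The section on statistical analysis defines the ICC to be reported as "mean rating (k = 2), absolute agreement, two-way mixed-effects model", with a 95% confidence interval. It classes ICCs with cut-offs at 0.5, 0.75 and 0.9, and removes cases with missing data listwise. Neither section says whether the planning value of 0.92 is a single-measure or a mean-of-two ICC, or whether 0.15 is a full width or a half-width.

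**The concern.** With two measurements per subject and an ICC close to 1, the sampling distribution of the ICC is skewed, and a symmetric large-sample width understates the interval obtained in a small sample. If 18 does not give 0.15, the precision stated for the first aim is not delivered at the number described as needed, and part of the step from 18 to 24 is required for precision and is not free to absorb dropouts. Listwise deletion means that each dropout lowers the analysed number directly.

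There is also a mismatch of form. The calculation sized a single-measure ICC, whereas the study will report the ICC of a mean of two. The width at a given number of subjects depends strongly on which of these the 0.92 describes.

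**Working it through.** **Inputs.** From the sample size section: ICC ρ = 0.92, k = 2, alpha = 0.05 (z = 1.96), w = 0.15, stated n = 18, recruitment 24. From the statistical analysis section: mean-of-two ICC, 95% interval.

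**1. The plan's own figure.** The large-sample formula for full width w is

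n = 8 z² (1 − ρ)² [1 + (k − 1)ρ]² / [k(k − 1) w²] + 1

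= 8 × 1.96² × 0.08² × 1.92² / (2 × 0.15²) + 1 = 17.11, rounded up to **18**.

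This matches the protocol. Reading 0.15 as a half-width gives 5.03, so 6 subjects; the full width is therefore what was used. At n = 18 the formula itself implies a width of 0.146.

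**2. F-based limits, single-measure ICC of 0.92.** The observed ratio is F₀ = (1 + 0.92)/(1 − 0.92) = 24. With F_L = F₀ divided by the upper 2.5% point of F, and F_U = F₀ multiplied by the corresponding point with degrees of freedom exchanged, each limit is (F − 1)/(F + 1). The degrees of freedom are (n − 1, n) for the one-way model and (n − 1, n − 1) for two-way consistency.

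At n = 18, one-way: F_L = 24/2.617 = 9.17 and F_U = 24 × 2.652 = 63.65. The limits are 0.803 and 0.969, a width of 0.166. Two-way: 0.800 to 0.969, width 0.170.

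| n | One-way width | Two-way width |
|---|---|---|
| 18 | 0.166 | 0.170 |
| 20 | 0.155 | 0.158 |
| 21 | 0.1501 | 0.153 |
| 22 | 0.146 | 0.148 |
| 24 | 0.138 | 0.140 |

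So 0.15 needs 21 (one-way, rounded) or 22. Adding a small-sample term of 5ρ = 4.6 to the formula in step 1 gives 21.71, so 22 as well.

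**3. Average over repeated samples.** Step 2 evaluates the width at an observed ICC of exactly 0.92. In simulation (200,000 draws per n, true ICC 0.92, one-way limits), the mean width is 0.180 at 18, 0.156 at 22, 0.151 at 23 and 0.147 at 24. The median is 0.166 at 18 and 0.146 at 22. The mean width thus falls below 0.15 only at 24.

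**4. The mean-of-two ICC that will be reported.** Its limits are 1 − 1/F_L and 1 − 1/F_U (two-way degrees of freedom).

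- If 0.92 is a single-measure value, the mean-of-two value is 2 × 0.92/1.92 = 0.958, with F₀ = 24. The width at n = 18 is 0.096.
- If 0.92 is already the mean-of-two value, F₀ = 1/(1 − 0.92) = 12.5. At n = 18 the limits are 0.786 and 0.970, a width of 0.184. The width is 0.1503 at n = 24 and 0.146 at n = 25.

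**5. Effect on the margin.** The implied margin is 24 − 18 = 6. For the single-measure ICC it becomes 24 − 21 = 3 or 24 − 22 = 2, so 3/6 to 4/6 of it is used. If 0.92 is a mean rating, nothing is left.

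**The case against.** The strongest reply is that 18 is not a miscalculation. The protocol discloses the function and the inputs, and they reproduce the result; what is at issue is how well a published planning approximation suits this setting. That stands.

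The second reply is that 0.17 and 21 to 22 do not describe the ICC the study will report. That also stands. If 0.92 is a single-measure value, the planned mean-of-two interval meets the target at 18 with room to spare. A reader might infer that every ICC interval in the study will be wider than promised. The documents do not support this, because they do not settle which form 0.92 takes. It is equally true that the favourable reading pairs a single-measure input with a mean-rating interval, which is not what the calculation sized.

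Third, a reader might infer that most of a planned 25% dropout allowance does not exist. The protocol states no dropout rate; six is only the difference between 24 and 18, and at 21 the loss is exactly half. The figure of 24 also rests on the ANOVA result, which this point leaves untouched.

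Fourth, a reader might infer that the interval at 18 covers the whole class labelled good (0.75 to 0.90). It does not: for a single-measure ICC its lower limit is about 0.80. It is only wider than that class, whose width is 0.15. At 21 subjects the interval (0.816 to 0.967, one-way) still straddles 0.90, so the classification would hardly change.

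**Conclusion.** The point holds in a limited form. For the single-measure ICC that was sized, 18 subjects give a 95% interval about 0.17 wide when evaluated at 0.92, and 0.15 needs 21 to 22. For the mean-of-two ICC that is planned, 18 is either ample (about 0.10) or clearly short (about 0.18, with about 0.15 at 24 and strictly 25 needed), depending on what 0.92 denotes.

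This corrects a precision statement and does not threaten the study: with 24 completers the single-measure width is about 0.14. The result assumes that 0.15 is a full width and that the interval is two-sided at 95%. The F-based limits used here ignore between-session variance, which would widen an absolute-agreement interval somewhat.

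**What to change.** Keep recruitment at 24 and revise the precision statement in the sample size section:

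- say whether 0.92 is a single-measure or a mean-of-two ICC, and that 0.15 is a full width;
- recompute with F-based limits for the ICC form named in the statistical analysis section;
- replace the claim that 18 suffices with the widths at 24 and at 18 completers. For a single-measure ICC these are about 0.14 and 0.17 evaluated at 0.92, or about 0.147 and 0.180 as means over repeated samples;
- say which of these two measures of width is meant. The number 22 should not be described as giving an *expected* width of 0.15, because the mean width there is about 0.156.

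The cost is one or two sentences and a short recalculation, with no further participants. The margin for dropouts will look smaller than it does now if 0.92 is a mean rating or if precision is still stated for the single-measure ICC.

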To assess the effects of different ISI on Vc during repeated stimulation, we will employ a within-subject repeated-measures ANOVA. The two independent variables will be ISI (10 s, 20 s, 30 s) and stimulus number (stimulus 1 to stimulus 10). The dependent variables will be Vc_0-10%_, Vc_0-90%_, Vc_10-90%_, Vc_norm_ and Vc_Dm/t90%_ for both the RF and BF, respectively. Pairwise comparisons with Bonferroni correction will applied for significant main effects. The effect size Cohen’s d will be calculated as d = M_diff_ / √SD_1_ + SD_2_ / 2 [53] for pairwise comparisons to allow comparisons between effects of different ISI and between consecutive stimuli. Thresholds for small, moderate, large, very large or extremely large effects will be 0.2, 0.6, 1.2, 2.0 and 4.0 [54].

Statistical significance will be set at alpha ≤ 0.05. Missing data will be handled by listwise deletion of cases with missing data [55]. All statistical analyses will be performed using R studio and respective packages. Upon completion of the data collection and analysis, the raw data disaggregated by sex and the analysis code will be openly available at https://osf.io/4du2j/?view_only=ee7a4afb30514cb9a2e15381282dcec8.

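### The ISI sample size is worked for a three-group between effect although ISI is tested within one group, and f = 1.6 for Vc_norm conflicts with the protocol's own report on Tc, so the stated 95% power is unsupported

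*Protocol article*

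**What the plan says.** The Sample size justification section takes raw data from an earlier ISI study, computes Vc_10-90% = 0.8 Dm/Tc and Vc_norm = 0.8/Tc, and says it estimated the main effect of ISI on both. The power inputs are then: "we assumed three groups, ten measurements per subject, an effect size f = 3.1 (Vc_10-90%_) and f = 1.6 (Vc_norm"). Coefficients for nonsphericity, 0.7 and 0.6 respectively, are added, and the remaining settings read "an alpha level of 0.01, a power of 0.95 and a between effect". From these the section arrives at "a total of 9 (Vc_10-90%_) subjects and 18 (Vc_norm_) subjects were needed". Together with a separate precision calculation for the ICC (18 subjects), this leads to a target of 24.

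The design is described differently elsewhere. Study design: "This study will be a single group reliability study". Experimental approach: each participant receives the 10 s, 20 s and 30 s blocks in random order. Statistical analysis: "we will employ a within-subject repeated-measures ANOVA", with ISI and stimulus number as factors and significance at 0.05.

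On the source study, the Introduction says: "One study investigated the effect of different ISI (30 s, 10 s, 5 s) on Dm and Tc of the RF muscle", and "The results showed that Tc was not significantly affected by different ISI". It adds that Dm was significantly greater at 10 s than at 30 s, and that Tc fell significantly over the ten stimuli. The Discussion repeats this.

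**The concern.** Two things do not fit together.

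- **The test.** A between effect with three groups compares different people under different ISIs. On that reading, 9 subjects means three per ISI. The planned test compares each person with himself or herself.
- **The effect size.** Vc_norm depends on Tc alone. A source that showed no significant ISI effect on Tc can hardly have shown an ISI effect explaining 72% of the partial variance in 0.8/Tc.

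The protocol attaches 95% power to the ISI aim and hopes to inform a standard procedure. If that power is not real, a non-significant ISI result would carry more weight with readers than it deserves.

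**Working it through.** **Inputs from the protocol.** Three groups; f = 3.1 with coefficient 0.7; f = 1.6 with coefficient 0.6; alpha 0.01; power 0.95; between effect; analysis alpha 0.05; target 24. The number of source subjects is not given, so a range is used.

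**Step 1: reproduce 9 and 18.** Between effect with three groups: df = 2 and N − 3, noncentrality λ = f² × N × coefficient, alpha 0.01.

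| f | coefficient | N | λ | power |
|---|---|---|---|---|
| 3.1 | 0.7 | 8 | 53.8 | 0.905 |
| 3.1 | 0.7 | 9 | 60.5 | 0.975 |
| 1.6 | 0.6 | 18 | 27.6 | 0.940 |
| 1.6 | 0.6 | 19 | 29.2 | 0.958 |
| 1.64 | 0.6 | 18 | 29.0 | 0.952 |

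The 9 is matched exactly. The 18 is matched if the unrounded f was about 1.64, which rounds to 1.6. So the wording about groups was also the calculation used.

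**Step 2: does the group structure undersize the study?** Keep the stated f and change only the test, to a three-level within-subject effect with df = 2ε and 2(n − 1)ε. The 95% requirement at alpha 0.01 becomes 5 (λ = f² × 2(n − 1)ε) or 6 (λ = f² × nε) subjects for f = 3.1, and 10 or 16 for f = 1.6. These are below 9 and 18, so the wrong test does not by itself undersize the study.

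**Step 3: what the f values mean as an ISI main effect.** Partial eta-squared = f²/(1 + f²).

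- f = 1.6: 2.56/3.56 = 0.72
- f = 3.1: 9.61/10.61 = 0.91

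For a three-level within-subject effect in n subjects, F = f²(n − 1) on 2 and 2(n − 1) df. For f = 1.6:

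| source n (assumed) | F | p, ε = 1 | p, ε = 0.6 | p, ε = 0.5 (most severe) |
|---|---|---|---|---|
| 4 | 7.7 | 0.022 | 0.055 | 0.069 |
| 5 | 10.2 | 0.006 | 0.023 | 0.033 |
| 10 | 23.0 | 0.00001 | 0.0004 | 0.001 |
| 20 | 48.6 | <0.000001 | <0.000001 | 0.000001 |

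From five source subjects upward, f = 1.6 would be significant under any nonsphericity correction. That is at odds with the reported result for Tc.

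**Step 4: largest f compatible with p > 0.05 in the source.** f_max = √(F_crit/(n − 1)).

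| source n (assumed) | ε = 1 | ε = 0.5 |
|---|---|---|
| 8 | 0.73 | 0.89 |
| 10 | 0.63 | 0.75 |
| 20 | 0.41 | 0.48 |

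These bound the effect on Tc. They carry over to 0.8/Tc approximately, because the reciprocal is not linear.

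**Step 5: what 24 subjects deliver.** One group, three-level within-subject test, df = 2ε and 46ε, λ = f² × 46ε, f the partial f of Step 3.

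| alpha | ε | power at f = 0.40 | power at f = 0.60 | f for 95% power |
|---|---|---|---|---|
| 0.05 | 0.6 | 50% | 84% | 0.73 |
| 0.05 | 1 | 65% | 95% | 0.60 |
| 0.01 | 0.6 | 25% | 62% | 0.88 |
| 0.01 | 1 | 39% | 84% | 0.71 |

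**The case against.** **f = 3.1 is not refuted.** A reader might infer that the protocol's account rules out both effect sizes. It does not. Vc_10-90% depends on Dm as well as Tc, and the protocol reports a significant Dm difference between 10 s and 30 s. A partial eta-squared of 0.91 is extreme and should be checked, but without the source's size and F values it stays possible. This stands.

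**The wrong test is conservative.** At the same f, a within-subject test needs fewer subjects. The nonsphericity coefficient, which has no role in a between effect, also pushes N up: without it the between formula gives 8 and 14. This stands, so the loss of the 95% claim cannot be blamed on the group structure.

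**The 5 s interval.** A reader might infer that including 5 s in the source inflated the effect. The only significant ISI contrast the protocol reports is 10 s against 30 s, both of which this trial uses. The sets of intervals differ (30, 10, 5 s against 10, 20, 30 s), but the direction of any bias is unknown.

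**The study is not set up to claim that ISI is irrelevant.** Its hypothesis is that Vc is affected by ISI. The risk of over-reading a null result is general and not a stated aim.

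**The detectable effect need not be very large on the plan's own scale.** With equally spaced means and sphericity, f = 0.73 in 24 subjects is a 10 s to 30 s difference of d_z = 0.73 × √2 × √(23/24), about 1.0 SD of the differences. The plan scales Cohen's d by the SDs of the conditions. Then d = d_z√(2(1 − r)), which is about 0.40 if the correlation r between ISIs is 0.92 (borrowed from the ICC input, an assumption), 0.78 if r = 0.7 and 0.32 if r = 0.95. So it would be wrong to say that 24 subjects can detect only very large effects.

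**The repeat run in a second program.** Repeating the calculation with the same f does not test that f. None of these points resolves the conflict between f = 1.6 and the Tc result.

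**Conclusion.** The passage is wrong as written, in two respects. First, 9 and 18 are derived from a between effect with three groups at alpha 0.01, while the trial tests ISI within a single group at 0.05. Second, f = 1.6 for Vc_norm, the input behind the larger ISI figure, conflicts with the protocol's report that ISI did not significantly affect Tc. This holds if the source had at least five subjects and if f is the partial ISI main effect that the text says it is. The reciprocal transformation is unlikely to bridge the gap. The values may belong to another effect, such as stimulus number, or to another type of eta-squared; the protocol does not show which.

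The 95% power for the ISI aim is therefore unsupported, because of f. The documents do not show that 24 subjects are too few: the true ISI effect on Vc is unknown, and the ICC calculation supports the number separately for the reliability aim.

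**What to change.** Withdraw the figures of 9 and 18 for the ISI effect. Re-check the source ANOVA and report F, degrees of freedom and type of eta-squared for the ISI main effect on both Vc measures, noting that the source intervals differ from the planned ones. An effect recomputed from 10 s and 30 s alone would be a two-level effect and should not be entered directly into a three-level power calculation.

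Keep 24 subjects and state what they deliver in a one-group, three-level within-subject test at the analysis alpha. For example: at 0.05, 95% power for a partial f of about 0.73 with epsilon 0.6 (0.60 with epsilon 1), and about 50% (65%) at f = 0.40. If 0.01 is meant to be the operative level, say so in the analysis section; the 95% thresholds are then 0.88 (0.71). Commit to reporting a non-significant ISI effect with its confidence interval and not as absence of an effect.

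The cost is one rewritten paragraph, no extra participants, and a less favourable power statement. The protocol plans preregistration before recruitment, so the correction belongs in that version.
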